### 2.8. Data Management Plan

In this trial, the Danish Data Protection Act will be complied with in addition to the General Data Protection Regulation (GDPR).

CRFs are completed for each subject enrolled in this study directly in REDCap (https://redcap.au.dk/), hosted at Aarhus University [28,29], to the extent possible without the use of a paper CRF. If a paper CRF is used, the data are subsequently entered into the electronic CRF in REDCap. REDCap is a secure, web-based software platform designed to support data capture for research studies, providing (1) an intuitive interface for validated data capture; (2) audit trails for tracking data manipulation and export procedures; (3) automated export procedures for seamless data downloads to common statistical packages; and (4) procedures for data integration and interoperability with external sources. Source documents include medical records, pain diaries, and CRFs. Manual personal identifiable data are kept securely locked. Data will be stored for 25 years in accordance with Good Clinical Practice (GCP) regulations. The study personnel are trained in the study procedures.

### 2.9. Sample Size Calculation

According to a previous double-blind, placebo-controlled study on intramuscular neridronate in patients with CRPS type 1, we expect an average reduction in pain intensity in patients with CRPS of 4 on an NRS (0–10) and a placebo response of 2 on the same scale. With a similar standard deviation in both groups (placebo and patients) of 2.5, a type 1 error rate of 5%, and a power of 80%, a sample size of 26 patients in each group yields a minimum detectable effect of 2 (0–10 NRS) [58]. As there are no comparable studies in CRPS, we aim for 26 patients in each group (30 to account for dropouts), as stated in the power calculation above. We will also accept 20 patients (with a power 70) and 23 patients (with a power 75) in each group, although with less power (calculation based on the same study).

### 2.10. Statistics

Baseline characteristics, including demographics and disease characteristics, will be described using means with the standard deviation (SD) or medians with the interquartile range (IQR) for continuous variables and numbers with percentages for categorial variables. We will use a flow chart to describe the inclusion of patients, including dropouts, loss to follow up, and missing data. We will also report the number of screen failures.

Statistical analysis of the primary outcome will be performed using a *t*-test (parametric) or Mann–Whitney U-test (non-parametric), where applicable. Non-dichotomous primary and secondary outcomes will be performed using a *t*-test or Mann–Whitney *U* test, where applicable. For the primary outcome, the delta values from the average pain intensity in the baseline week to the last treatment week (last 7 days) will be used. Response rates and other dichotomous data are analyzed using Fisher’s exact test or χ^2^ test. Spearman’s correlations coefficient will be used to assess predictors.

The analysis for the primary outcome is the intention-to-treat (ITT) population. The last observation carried forward (LOCF) will be the primary imputation method, and the baseline observation carried forward (BOCF) will be used as a secondary imputation method for those that do not finish the pain diary. Missing data will not be replaced. All patients who have received at least one injection will be encouraged to stay in the study, complete the diary, and come for the remaining visit after 4/8 weeks.

Significance is considered at the 5% level. If there are changes to the original statistical plan, the type of change and the date of the change will be documented, and the document will be signed by the sponsor.

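### The primary test is stated as either a t-test or a Mann–Whitney test with no rule for choosing; fix one analysis, a baseline-adjusted mean difference, before unblinding

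*Protocol article*

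**What the plan says.** Section 2.10 (Statistics) gives the primary analysis as a t-"test (parametric) or Mann–Whitney U-test (non-parametric), where applicable". The next sentence repeats the same alternative for the non-dichotomous primary and secondary outcomes. The variable analysed is fixed: "the delta values from the average pain intensity in the baseline week to the last treatment week (last 7 days) will be used". So is the level: "Significance is considered at the 5% level". The section also says that changes to the original statistical plan will be documented, dated and signed.

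Section 2.9 (Sample Size Calculation) sizes the trial on means. It expects an "average reduction in pain intensity in patients with CRPS of 4 on an NRS (0–10) and a placebo response of 2" and continues "With a similar standard deviation in both groups (placebo and patients) of 2.5". With "a type 1 error rate of 5%, and a power of 80"%, it concludes that "a sample size of 26 patients in each group yields a minimum detectable effect of 2" NRS points. It also accepts 23 or 20 per group at stated powers of 75% and 70%. It names no test.

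Section 2.5 stratifies the randomisation by sex.

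**The concern.** Two tests are allowed for the one outcome that decides the trial. They are not two routes to the same answer. The t-test addresses a difference in mean change, the quantity on which section 2.9 is built. The Mann–Whitney test addresses whether values in one arm tend to exceed those in the other, and it does not itself estimate a difference in NRS points.

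Because either test satisfies the text, the choice could be made after the unblinded data are seen without counting as a change to the plan. The commitment to document changes would then not be triggered. In a trial of this size the two tests can fall on opposite sides of 5%, so the reported conclusion could depend on which one is used.

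**Working it through.** **1. Inputs**

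- From section 2.9: difference 4 − 2 = 2 NRS points, SD 2.5 in both arms, type I error 5%, power 80%, 26 per group (fallbacks 23 and 20; 30 per group with dropouts).
- From section 2.5: 1:1 allocation.
- Assumed: two-sided testing, since the article does not state sidedness. A one-sided 5% test would give about 89% power at 26 per group, so two-sided is what the stated size implies.
- Assumed: every non-normal shape below, since the article gives no distribution for the change scores.

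**2. Reproducing the stated sizes with a t-test**

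The noncentrality is δ = 2 / (2.5 × √(2/n)) with 2n − 2 degrees of freedom.

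| n per group | δ | Exact t-test power | Stated power |
|---|---|---|---|
| 26 | 2 / (2.5 × 0.2774) = 2.88 | 80.7% | 80% |
| 23 | 2 / (2.5 × 0.2949) = 2.71 | 75.6% | 75% |
| 20 | 2 / (2.5 × 0.3162) = 2.53 | 69.3% | 70% |

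All three stated sizes reproduce. The sample size is that of a two-sided comparison of means.

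**3. Mann–Whitney power on the same inputs, normal data**

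- Simulation (100,000 trials): 78.4% at 26 per group, 72.7% at 23, 67.0% at 20 and 83.9% at 30.
- Relative efficiency 3/π = 0.955: t-test power at an effective 26 × 0.955 per group is 78.9%. The size needed for 80% is 26 / 0.955 = 27.2, so 28 per group.
- Noether's formula: p = Φ(2 / (2.5√2)) = 0.714, and N = (1.960 + 0.842)² / (12 × 0.25 × (0.714 − 0.5)²) = 57.0 in total, so 29 per group.

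The shortfall at 26 per group is 1 to 2 points.

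**4. What the open choice could do**

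Simulation at 26 per group with SD 2.5: 100,000 trials for the normal shape and 20,000 for each other shape. The third column counts a trial as significant if either test gives p < 0.05.

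| Shape | Type I error, each test alone (t / MW) | Type I error, smaller p reported | Tests disagree at difference 2 | Power at difference 2 (t / MW) |
|---|---|---|---|---|
| Normal | 4.9% / 4.8% | 5.7% | 5.3% | 80.8% / 78.4% |
| Laplace | 4.9% / 4.9% | 6.5% | 9.4% | 81.3% / 89.4% |
| Exponential | 4.9% / 4.8% | 6.8% | 13.9% | 81.0% / 94.5% |
| Uniform | 5.2% / 4.9% | 5.7% | 6.9% | 81.0% / 74.4% |

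**5. Choice by a fixed rule**

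The rule was: Mann–Whitney if a Shapiro–Wilk test rejects at 5% in either arm, otherwise the t-test. Over 6,000 null trials per shape, the type I error was 4.9% for normal data and 5.0% for exponential data. A rule fixed in advance therefore does not materially raise the error. The excess in step 4 comes from choosing on the p-values.

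**The case against.** The strongest reply has four parts.

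- **The natural reading is harmless.** The labels parametric and non-parametric suggest a choice by distribution, and step 5 shows that a fixed rule of that kind holds 5%. This stands. A reader might infer that any look at the data breaks the error rate, or that the trial intends to run both tests and report the better one. The article supports neither. The 6–7% figures describe selective reporting, which the wording permits but does not announce.
- **A rule may be in the unseen plan.** Section 2.10 refers to an original statistical plan, and an article condenses. This also stands, so the point can only say that this text shows no rule. If one exists, citing it answers the complaint about open choice. It would not by itself tie the result to the quantity the trial was sized on.
- **The Mann–Whitney option is not underpowered in any way that matters.** A reader might infer that it fails the stated 80%. Under normality the loss is 1 to 2 points at 26 per group, and power is about 84% if all 30 per group are analysed. For the heavy-tailed or skewed shapes where the test would mainly be used, power is 89–95%. Only the flat, uniform-like shape falls clearly short, at about 74%. The power criticism is not made.
- **This is a proof-of-concept study, and a rank p-value can be accompanied by a mean difference or a Hodges–Lehmann shift.** Both are true and they lower the stakes. They do not settle which result decides the primary objective when the two disagree.

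**Conclusion.** The point holds in a limited form. Section 2.10 states two primary tests with different hypotheses and shows no way of choosing between them. Only the mean difference corresponds to section 2.9, whose three sizes reproduce for a two-sided t-test.

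The cost is modest. Type I error rises by roughly 0.7 to 1.8 points above the nominal 5%, and only if the more favourable p-value is the one reported. Under the planned effect the tests disagree in about 5% of normal trials and about 9–14% of Laplace or exponential trials. The non-normal figures depend on assumed shapes and all figures assume two-sided testing. The conclusion about the missing rule is limited to the article.

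This should be corrected, but it does not threaten the design.

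**What to change.** Before unblinding, name one primary analysis in section 2.10: the between-group mean difference in change in average daily pain from baseline to week 8, with its 95% CI, from an ANCOVA adjusted for baseline-week pain and for sex, the stratification factor. State that it applies whatever distribution is observed. Name the Mann–Whitney test as a sensitivity analysis that cannot replace the primary result.

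This targets the quantity in section 2.9 and uses data already collected. It also takes account of baseline pain and of the stratified randomisation, which neither listed test on the change scores does.

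The cost is a short amendment, dated and signed as section 2.10 already provides. Inclusion is expected to run until July 2027 (section 3), so there is time. The downside is some loss of efficiency against a rank test if the change scores are heavily skewed: in the assumed exponential case the unadjusted comparison is 81.0% power for the t-test against 94.5% for the Mann–Whitney test.

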### 2.3. Study Visits

All visits are planned at the beginning of the study. Visit 2 is defined as day 1. All study visit days are calculated from this visit date (Table 1).

At visit 1 (screening visit), the patient sits down with a member of the study team, discusses any additional questions, and provides informed consent. After informed consent is obtained, the patient is further assessed for study eligibility. Previous and current medical histories are obtained, and focused neurological and physical examinations are performed to establish or confirm the CRPS diagnosis, and for fertile women, a pregnancy test is taken. The patients are trained to report pain intensity.

Registration in the pain diary starts in the baseline period. If visit 1 is scheduled for more than seven days before visit 2, the patients are instructed to fill out the pain diary for the last seven days minimum preceding visit 2. The patients should have an average daily pain (ADP) intensity of at least 4 and not above 9 on a numeric rating scale (NRS) from 0 to 10 (0 = no pain; 10 = worst possible pain) in the baseline period. This is not revealed to the patient.

At visit 2, the pain diary is used to confirm the inclusion and exclusion criteria (Table 2). Patients are, thereafter, randomized to treatment with fremanezumab or placebo. They receive the first dose of the study drug, and outcomes are accessed (see section on outcomes). Registration in the pain diary continues until the last week of treatment (week 8).

At visit 3, after four weeks of treatment, patients receive the second dose of treatment. An assessment of concomitant medication and any potential side effects is conducted, and blood pressure and pulse are measured. Additionally, a questionnaire on pain relief is filled in. Patients will not receive the second dose of study medicine if the side effects are unacceptable or if they wish to stop for other causes, but all patients who have taken at least one of the two doses of study drug or placebo are asked to continue to participate in the study as described below.

At visit 4, after the treatment period of eight weeks, outcomes are assessed again. An assessment of concomitant medication and any potential side effects and completion of the study is also conducted.

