### 2.5. Randomization and Blinding

Randomization is carried out at a 1:1 rate, stratified by sex, via computer-generated randomization in REDCap using block sizes unknown to the investigators. Randomization is carried out after the baseline period if the patients meet the criteria of at least 4 on an NRS from 0 to 10.

It is not possible to make the active drug and placebo syringes identical in appearance, and they are, therefore, prepared and administered by two unblinded third-party personnel (to ensure double control) at the study site. The active substance comes in a package from the manufacturer, and the information on the package is not covered by a research label. The placebo (isotonic saline) is prepared on the study site in a separate room from where the subject receives the treatment. The needles are identical, and the subject is blindfolded during the injection. Hence, the study is double-blind (patients, health care providers, and investigators/study personnel). The sequence of the randomization numbers is only available to the unblinded personnel. The code for randomization is stored in a locked room until the study is completed. For each randomization code, there is a sealed envelope with information on the treatment given. The code envelope is only unsealed/opened if continued treatment requires knowledge of the randomization code.

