### 2.7. Outcomes

Primary outcomes are as follows:1.Difference between groups (placebo vs. active treatment) in the change in self-reported daily ratings of mean ADP intensity in the affected limb from the baseline week (week −1) to the last week of treatment (week 8), as experienced during the past 24 h, rated on an 11-point NRS from 0–10 (0 = no pain; 10 = worst possible pain): the primary outcome is validated and recommended as a first Core Outcome Measurement set for complex regional PAin syndrome Clinical sTudies (COMPACT) and a standard measure of chronic pain in clinical trials [33,34,35,36].

Secondary outcomes are as follows:Difference in pain relief on a 6-point scale—complete, good, moderate, mild, none, or worse—assessed at visits 3 and 4.Difference in the change in the mean CRPS Severity Score (CSS) from the end of baseline to the end of weeks 4 and 8: CSS scores will also be divided into two sub-categories: symptoms and signs [37,38] (assessed at visits 2–4).Differences in the area and intensity of mechanical allodynia, assessed by brushing a soft brush (Somedic) twice at a speed of 1–2 cm/s: the area is measured in cm and the intensity rated on an NRS (0–10) and compared to the unaffected site (assessed at visits 2–4).The relationship between the primary outcome measure and the duration of CRPS (measured in months).

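### The primary test on change scores fixes the baseline slope at 1 and leaves out the sex stratum; it is valid, but an ANCOVA would probably be more precise at almost no cost

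*Protocol article*

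**What the plan says.** Section 2.10 names the test: "Statistical analysis of the primary outcome will be performed using a *t*-test (parametric) or Mann–Whitney U-test (non-parametric), where applicable". It also names the quantity tested: "the delta values from the average pain intensity in the baseline week to the last treatment week (last 7 days) will be used". It gives no covariate, regression model or stratified test, and it applies the same pair of tests to the non-dichotomous secondary outcomes.

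Two pieces of pre-randomisation information are available for that comparison. Section 2.5 states: "Randomization is carried out at a 1:1 rate, stratified by sex". Section 2.3 has patients "fill out the pain diary for the last seven days minimum preceding visit 2", so a baseline-week mean should exist for every randomised patient. Nowhere does the article use sex or baseline pain as an adjustment in the primary comparison.

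Among the secondary outcomes in Section 2.7, the CRPS Severity Score is defined as a change from baseline. Allodynia is worded only as "Differences in the area and intensity of mechanical allodynia, assessed by brushing a soft brush", although it is assessed at visits 2 to 4 and so has a baseline value.

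**The concern.** Analysing change is the same as adjusting for baseline with a coefficient of exactly 1. That is efficient only if week-8 pain rises one for one with baseline pain within each group. Here there is reason to expect less. Entry requires a baseline mean of at least 4, so some regression to the mean is likely, and Section 4 notes that symptoms fluctuate and some patients remit. With a slope below 1, change is correlated with baseline, and the part of its variance that baseline could explain stays in the standard error.

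Leaving out sex has a separate effect. Stratification balances sex between the arms, but a test that ignores the stratum still counts any sex difference as noise, so its true type I error falls a little below 5%.

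Precision matters in this trial. Section 2.9 aims for 26 evaluable patients per group but accepts 20 at 70% power, and Section 4 warns that recruitment may fall short.

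**Working it through.** **Inputs from the article.** Section 2.9: difference of 2 NRS points (reduction of 4 against 2), SD 2.5 in each group, type I error 5%, power 80%; 26 per group, with 23 (75%) and 20 (70%) also accepted. Section 2.3: baseline mean pain from 4 to 9.

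**Assumptions.** The 2.5 is taken as the SD of change, because the expected values are reductions. The test is two-sided. Baseline SD is 1.2 to 1.8; for comparison, a uniform spread over 4 to 9 has SD 5/√12 = 1.44. The within-group slope *b* of week-8 on baseline pain is 0.3 to 1.0. The article gives neither the baseline SD nor the slope.

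**Step 1: reproduce the plan's figures.** For an unadjusted two-sample t-test, the noncentrality is 2 / (2.5 × √(2/n)) on 2n − 2 degrees of freedom.

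- n = 26: 2 / 0.693 = 2.884 on 50 df, power 80.7%
- n = 23: 2.713 on 44 df, power 75.6%
- n = 20: 2.530 on 38 df, power 69.3%

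These match the stated 80, 75 and 70%. The sample size therefore assumes no adjustment.

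**Step 2: ANCOVA.** The residual variance is 2.5² − (1 − b)² × SD_baseline². The variance of the treatment difference is multiplied by 1 + 1/(2n − 4) for estimating the slope. Degrees of freedom are 2n − 4, for baseline and sex. No gain from sex is credited here.

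Central case (SD 1.5, b = 0.5): 6.25 − 0.25 × 2.25 = 5.6875, residual SD 2.385. At n = 26 the inflation is 1 + 1/48 = 1.0208, and the noncentrality is 2 / (2.385 × √(2/26 × 1.0208)) = 2.993 on 48 df, so power is 83.5%.

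| Baseline SD | Slope | Residual SD | Power, 26 per group | Power, 20 per group |
|---|---|---|---|---|
| (unadjusted) | fixed at 1 | 2.500 | 80.7% | 69.3% |
| 1.8 | 0.3 | 2.159 | about 90% | 80.3% |
| 1.5 | 0.3 | 2.269 | 86.9% | 76.3% |
| 1.5 | 0.5 | 2.385 | 83.5% | 72.1% |
| 1.2 | 0.7 | 2.474 | 80.7% | 68.9% |
| 1.5 | 0.9 | 2.495 | 80.0% | 68.2% |
| any | 1.0 | 2.500 | 79.9% | 68.0% |

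In the central case 24 per group reach 80%, against 26 unadjusted.

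**Step 3: sex alone.** Assume 75% women and a sex difference in change of *d* points. The variance explained is 0.75 × 0.25 × d² / 6.25, which is 0.8% at d = 0.5 and 6.8% at d = 1.5. Adjusting for sex with one df gives 81.0% to 83.3% power at 26 per group. Ignoring it, the nominal 5% test runs at about 4.9% down to 4.2%.

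**Step 4: a chance imbalance.** With baseline SD 1.5, the standard error of the baseline difference at 26 per group is 1.5 × √(2/26) = 0.42. If the arms differ by that much and b = 0.5, the change-score estimate is shifted by (1 − 0.5) × 0.42 = 0.21 points. ANCOVA removes this shift.

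**The case against.** The planned test is valid, matches its own sample-size calculation and contradicts nothing in the article. It does use baseline, by subtracting it. The baseline SD and the slope are not given, so the gain cannot be fixed, and restricting entry to 4–9 makes a steep slope possible. Once the cost of estimating the slope is charged, the central gain is only about 3 points at either sample size, and near slope 1 it turns into a small loss. All of that stands, and it is why the range above runs to slope 1.0.

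A linear model may also suit allodynia area and intensity poorly if they are skewed or have many zeros. The article's rank test has a purpose there, so the fix needs a rank-based alternative. A condensed article may also simply have left out the word change for allodynia, so its wording does not show that the visit 2 value will go unused.

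One defence does not stand: that this is detail for a statistical analysis plan. Section 2.10 already names the primary test and the quantity tested, so a plan that used ANCOVA as primary would depart from it.

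**Conclusion.** The point holds as one of efficiency, not validity. Under the stated assumptions ANCOVA takes power at 26 per group from 80.7% to about 80–90%, and at 20 per group from 69.3% to about 68–80%. The worst case is a loss of about 1 point. The choice favours ANCOVA because the possible loss is small and the possible gain much larger, not because a large gain is assured.

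Three stronger readings are tempting, and the documents do not support them:

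- **That the analysis ignores baseline pain.** This is true of sex only. For baseline, what is missing is an estimated slope.
- **That the change-score estimate is biased.** Over randomisation it is not. The 0.21-point shift is conditional on an assumed imbalance and an assumed slope.
- **That adjustment would bring power to 87–94% at 26 per group.** Those figures arise if baseline and week-8 SDs are equal and their correlation is 0.3 to 0.7. With an SD of change of 2.5, the baseline SD would then be 2.5/√(2(1 − r)): 2.11, 2.50 and 3.23 at r = 0.3, 0.5 and 0.7. Values confined to 4–9 cannot have an SD above 2.5, even with half the patients at each end.

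**What to change.** In Section 2.10, prespecify as the primary analysis a linear model (ANCOVA) of week-8 mean average daily pain on treatment, baseline-week mean average daily pain and sex. Modelling the change instead gives the same treatment effect once baseline is in the model. Report the adjusted mean difference with its 95% confidence interval, and keep the unadjusted t-test or rank test as supportive.

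Use the same approach, each outcome with its own baseline, for the CRPS Severity Score and, where the distribution allows, for allodynia area and intensity with the visit 2 value as baseline. Where it does not allow, use a rank-based version.

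The cost is a few sentences and two degrees of freedom. No new data are needed. Section 2.10 already provides for dated and signed changes to the statistical plan, and Section 3 expects inclusion to run to July 2027, so there should be time to make the change before unblinding.
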